### Preschool recruitment

We will recruit participants from 24 preschools in China, 14 in Yang County, Shaanxi Province and 10 in Shicheng County, Jiangxi Province. Only preschools with more than 150 enrolled students will be eligible for this study; almost all preschools in the study sites are this size or larger, therefore the exclusion criteria for preschool size will have minimal impact on generalizability of results.

Each invited preschool will receive an official invitation letter along with relevant materials concerning the study. We will randomly allocate enrolled preschools rather than classes or individuals to the intervention group versus control group to avoid undesirable contamination within the same preschool. Thus, 12 preschools will be randomly allocated to the intervention group and 12 to the control group (Figs. 1 and 2).

**Fig. 1 Fig1:**
[figure not shown]
Flow diagram of selection of study participants

**Fig. 2 Fig2:**
[figure not shown]
Timeline for the schedule of enrollment, interventions, and assessments

### Participant recruitment

Eligible participants meet the criteria: being the primary caregiver of a preschooler attending the included schools.

Potential participants will be excluded from this study if they meet any of the following criteria: (1) unwilling to participate in this study; (2) do not own a smartphone or cannot operate the app independently; (3) cannot read text messages; or (4) expect to move to another city with their children during the study time period. If an eligible caregiver care for more than one eligible preschooler, we will enroll only the youngest child.

In coordination with local cooperative partners (governmental departments and agencies), we will recruit class teachers and school staffs to help coordinate recruitment of study participants in each selected preschool. Those individuals will inform eligible caregivers about the study via multiple existing preschool-family communication channels, such as social media platforms (WeChat or QQ), school apps, printed briefing materials and oral notification. Caregivers who agree to participate will be provided an invitation letter that includes the benefits and responsibilities of participating in this study and instructions to download, install, sign up, log in and use the randomly-assigned app. Moreover, all caregivers who agree to participate will receive a short online guidance video that detailedly introduces basic information about the study and educates the participants on how to utilize the app.

When participants log into the app for the first time, they will be invited to complete and submit the informed consent documentation online. All consenting participants will then complete the baseline survey, which collects information about unintentional injuries the child experienced in the past 3 months as well as information on socio-demographic characteristics, caregiver’s attitudes, caregiver-reported behaviors surrounding child unintentional injury prevention, and caregiver-reported home environment safety based on the standardized safety checklist over the prior week.

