### Randomization and blinding

Once recruited, each enrolled preschool will be randomly allocated to a group according to the order of computer-generated random number sequence by an independent (masked) researcher. Group allocation will be concealed during data analysis.

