### Collection of formal data

Survey data will be collected at baseline and every 3 months during the entire 18-month follow-up period. All data will be collected online through the app and stored in a password-protected backend database. If caregivers fail to complete an app-based online survey, designated members of the coordinating group will remind or guide them. When needed, a phone-based survey interview will be employed.

Participant engagement data will be gathered and stored in the backend database automatically through embedded tracking of app usage. Data to be collected include: (1) the frequency of logins, (2) time span from login to logout each time, (3) frequency of reading instructional materials, (4) time spent on learning instructional materials, (5) number of reading or bookmarking knowledge disseminations, (6) number of posting comments on knowledge disseminations, (7) number of likes clicked on knowledge disseminations, (8) frequency of joining a discussion in the online forum, (9) number of bookmarked online forum themes, (10) number of comments posted in the online forum, and (11) number of likes clicked in the online forum.

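### Caregivers consent and complete the baseline survey inside the assigned app, after their preschool has been allocated, so the plan leaves a risk of post-randomisation selection that its analysis cannot remove

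*Protocol article*

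**What the plan says.** All of this is in the Methods of the protocol article.

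- *Randomization and blinding*: "Once recruited, each enrolled preschool will be randomly allocated to a group". The trigger is recruitment of the preschool. An independent, masked researcher makes the allocation. The only concealment described is at the end of the trial: "Group allocation will be concealed during data analysis".
- *Participant recruitment*, on who recruits: "we will recruit class teachers and school staffs to help coordinate recruitment of study participants in each selected preschool". These people tell caregivers about the study. Caregivers who agree get a letter with "instructions to download, install, sign up, log in and use the randomly-assigned app".
- *Participant recruitment*, on consent: "When participants log into the app for the first time, they will be invited to complete and submit the informed consent documentation online".
- *Participant recruitment*, on baseline: "All consenting participants will then complete the baseline survey, which collects information about unintentional injuries the child experienced in the past 3 months". The same survey covers attitudes, supervision behaviour and home safety.
- *Collection of formal data*: "All data will be collected online through the app and stored in a password-protected backend database".
- *Interventions*: the app's four modules are the same in both arms. Controls receive a parenting health programme, and the intervention arm receives that programme plus injury-prevention content. Apart from content, delivery is the same.
- *Data analysis plan*: the GEE adjusts for socio-demographic variables, engagement and baseline injury events.

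*Study design* calls the trial single-blind but does not say who is blinded.

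**The concern.** In a cluster trial, randomisation balances the clusters. It protects the comparison of individuals only if those individuals are identified and enrolled before allocation is known, or by people who do not know it. Here the preschools are randomised, but the analysed caregivers join afterwards, through teachers and staff of an already allocated preschool. Two of the exclusion grounds, unwillingness and inability to use the app unaided, leave room for choice or judgement at that stage.

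If the caregivers who enrol differ between arms in their children's underlying injury risk, the primary comparison is shifted, and a larger sample does not help. Baseline values are exposed too. The injury history used for adjustment and the starting point for change in the secondary outcomes are both collected after allocation.

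**Working it through.** **Order of steps**

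1. The preschool is recruited, then allocated (*Randomization and blinding*).
2. Teachers and staff inform caregivers (*Participant recruitment*).
3. Caregivers who agree receive the letter for the assigned app. Describing the app as assigned presupposes that step 1 is complete.
4. Consent is given at first login to that app.
5. The baseline survey follows consent.

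Steps 4 and 5 therefore follow allocation on the article's own wording. For step 2 this is only an inference, because a first verbal agreement could precede allocation. No text says that it does, and formal enrolment would still come later.

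**What the stated safeguards cover**

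- Concealment during analysis masks the analyst, not recruiters or caregivers.
- The masked researcher protects the assignment of preschools, not the enrolment of caregivers.
- Intention-to-treat analysis starts from caregivers who consented, so it cannot see selection before consent.
- Adjustment for baseline injury handles that one measured factor, itself recorded after allocation. It does not handle unmeasured differences in who enrolled.

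**Size, for illustration only**

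The inputs from *Sample size* are 30% incidence over 18 months, ratio 0.80 (so 24%), ICC 0.005, 150 children per preschool, 15% attrition, 80% power and N = 3508. The plan's figure reproduces:

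- Design effect: 1 + (150 − 1) × 0.005 = 1.745.
- Unpooled two-proportion formula: 855.5 per arm. Total: 2 × 855.5 × 1.745 / 0.85 ≈ 3513. The pooled version (859 per arm) gives 3527. The stated 3508 agrees with both to within about 0.5%.
- Effective number per arm at N = 3508: 1754 × 0.85 / 1.745 ≈ 854, with power of about 80%.

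Now assume, without support from the documents, that enrolment changes the intervention arm's underlying risk by 5% or 10% relative to control. Observed ratio = 0.80 × (1 ± imbalance):

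- 5%: 0.80 × 0.95 = 0.76; 0.80 × 1.05 = 0.84.
- 10%: 0.80 × 0.90 = 0.72; 0.80 × 1.10 = 0.88.

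The shifts are 0.04 / 0.20 = 20% and 0.08 / 0.20 = 40% of the planned reduction.

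For the probability of declaring benefit, use Φ(d / SE − 1.96), with SE = √[(p₁(1 − p₁) + p₂(1 − p₂)) / 854] and p₁ = 0.30:

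| Assumed situation | p₂ | d / SE | Probability |
|---|---|---|---|
| True 0.80, seen as 0.84 | 0.252 | 0.048 / 0.0216 = 2.22 | about 60% |
| True 0.80, seen as 0.88 | 0.264 | 0.036 / 0.0218 = 1.65 | about 38% |
| No effect, seen as 0.95 | 0.285 | 0.015 / 0.0220 = 0.68 | about 10% |
| No effect, seen as 0.90 | 0.270 | 0.030 / 0.0218 = 1.37 | about 28% |

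The first two rows compare with the planned 80%. The last two compare with a nominal 2.5% in that direction.

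**The case against.** The strongest reply is that this is not a comparison of an app with no app. Controls are offered an active parenting programme with the same modules, rewards and support, so the usual driver of differential uptake, an unattractive control arm, is weak. Nothing shown says that the letter, the guidance video or the first-login screen reveals the arm. The baseline survey comes directly after consent, and no text describes exposure to content before it. The flow diagram and timeline figures are not reproduced and might show more about timing.

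Much of this stands, and it lowers the risk. It does not remove it. The article does not say that recruiters and caregivers are unaware of the arm, nor that content is locked before the survey. A timeline figure would not change the statement that consent is given inside the assigned app.

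A reader might go further and infer that enrolment or the baseline answers are already biased by arm. The documents do not support that: it would need knowledge of the arm or early access to content, and neither is stated. A reader might also take baseline attitude and home-safety scores to be adjustment covariates. The *Data analysis plan* names only injury events among the baseline outcome measures; the other scores are secondary outcomes.

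**Conclusion.** The point holds as a risk built into the stated sequence. Formal consent and baseline follow preschool allocation, and the only stated concealment is at analysis. This is not a gap left by condensing the protocol into an article, because the article itself sets the order. An analysis plan could not repair it, because it concerns conduct.

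The size and direction of any bias are unknown. The 20% to 40% shift and the probabilities above rest entirely on an assumed 5% to 10% imbalance in underlying risk. They show what such an imbalance would do, not what is expected here. The conclusion about sequence depends on reading the assigned app as one whose arm is already fixed when the letter goes out, which is the natural reading of the text.

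**What to change.** In each preschool, complete caregiver consent and the baseline survey in a common, arm-neutral app before that preschool's allocation is generated or released to recruiters and caregivers. Unlock arm-specific learning content only afterwards. If allocation must come first, keep recruiters and caregivers unaware of it, use the same consent and baseline forms in both arms, and lock content until the survey is submitted; the protocol should say so. In either case, state who is blinded and report the number of caregivers approached and enrolled per preschool by arm.

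The cost is a short delay before content is released and a content switch in the app. Because only learning content differs between arms, the switch should be modest work, but how easy it is depends on the app design, which is described in a separate publication that is not shown.

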### Randomization and blinding

Once recruited, each enrolled preschool will be randomly allocated to a group according to the order of computer-generated random number sequence by an independent (masked) researcher. Group allocation will be concealed during data analysis.

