### Sample size

Based on previous literature [29], we conservatively hypothesize that the unintentional injury incidence of rural preschoolers aged 3–6 years old in project sites is 30% in the past 18 months. On the basis of a previous report [30], we assume the effect size of the app intervention to be 0.80 (incidence rate ratio) compared to traditional unintentional injury prevention intervention. In addition, we assume an intra-class correlation (ICC) of 0.005 with a cluster size of 150 children per preschool [31], and an allocation ratio of 1:1 between intervention and control groups. Considering extensive strategies will be adopted to increase retention in the study, we assume an attrition rate of 15% for the 18-month follow-up. Given these assumptions, a minimum sample size of 3508 caregivers is needed for the study to achieve a statistical power of 80% at the 0.05 significance level. As many rural preschools have more than 150 children in the study sites we select, 24 preschools will be ample to recruit the needed sample size.

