### Data analysis plan

Primary data analysis will follow an intention-to-treat (ITT) approach. Descriptive statistics will be calculated for socio-demographic variables and primary and secondary outcomes, including mean (or median) and standard deviation (or range and interquartile range) for continuous variables, and frequency and proportion for categorical variables. For each time point, Chi-square and two-sample *t*-tests (or Wilcoxon rank sum test if data are skewed) will be used to examine the differences in outcome measures between intervention and control groups for categorical and continuous variables, respectively. Trend tests or analysis of variance (ANOVA) will used to detect within-group differences across the six follow-up visits.

Generalized Estimating Equation (GEE) will be used to assess the overall effectiveness of the app-based intervention, while adjusting for socio-demographic variables, engagement, and baseline injury events.

A Generalized Linear Mixed Model (GLMM) will be used to verify the GEE results. With GLMM, missing values can be imputed using the Expectation Maximization (EM) algorithm. A per-protocol (PP) sensitivity analysis will be conducted to validate ITT results. All statistical analyses will be performed using R version 4.0.4. All statistical tests will be two-sided at the significance level of 0.05.

Subgroup analyses will be conducted to assess the impact of socio-demographic factors on the intervention effect, including gender and age of children and their caregivers, type of children’s caregivers (e.g., parents, grandparents, or others), education level of caregivers, and household income per capita per month. Subgroup analyses will employ the same statistical methods used for the primary analyses.

This study will strictly adhere to the Consolidated Standards of Reporting Trials (CONSORT) 2010 statement [37] and the Standard Protocol Items: Recommendations for Interventional Trials (SPIRIT) 2013 statement [38] to analyze the data and report the results.

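### The article states no stratification by county for the 24 preschools and does not name county as a covariate, so county balance may be left to chance

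*Protocol article*

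**What the plan says.** Under Preschool recruitment, the protocol article recruits "14 in Yang County, Shaanxi Province and 10 in Shicheng County, Jiangxi Province". The unit of randomisation is the preschool, and the only balance stated is the overall one: "12 preschools will be randomly allocated to the intervention group and 12 to the control group".

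The method is given under Randomization and blinding: "each enrolled preschool will be randomly allocated to a group according to the order of computer-generated random number sequence by an independent (masked) researcher". Neither section mentions strata, blocks, matching or constrained allocation.

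Under Data analysis plan, the GEE is fitted "while adjusting for socio-demographic variables, engagement, and baseline injury events". The socio-demographic set is not itemised for that model. The factors listed for subgroup analyses are person- and household-level, "including gender and age of children and their caregivers, type of children’s caregivers (e.g., parents, grandparents, or others), education level of caregivers, and household income", and county is not one of them.

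The Sample size section works with a single control incidence, stating that injury incidence "in project sites is 30% in the past 18 months", and an incidence rate ratio of 0.80. It makes no separate allowance for county.

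**The concern.** County is known before randomisation and could plausibly affect the outcome. The two counties lie in different provinces. The engagement strategy runs through local education, health and disease-control bodies, so support and follow-up may differ between them. The article itself treats county as a design unit in the pilot, which takes 30 caregivers from each.

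With only 12 preschools per arm, randomisation cannot be relied on to even out a two-level site factor. If one arm draws more preschools from the higher-incidence county, the realised arm difference moves by an amount unrelated to the app. Over repeated allocations this averages out, but it adds variance to the estimate. Stratification is also a design step: no later analysis document can restore it once the preschools are allocated, although a county term in the model can do much of the same work.

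**Working it through.** **1. The plan's own sample size.** Inputs from Sample size: 30% control incidence; ratio 0.80, hence 24% and a 6-point target difference; ICC 0.005; cluster size 150; attrition 15%; power 80%. The two-sided 0.05 level is in Data analysis plan.

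- Design effect: 1 + (150 − 1) × 0.005 = 1.745.
- Per arm, unpooled variance: (1.96 + 0.842)² × (0.30 × 0.70 + 0.24 × 0.76) / 0.06² = 855.5.
- Total: 2 × 855.5 × 1.745 / 0.85 = 3513. The pooled-variance version, 859 per arm, gives 3527.

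The stated 3508 is reproduced to within 0.1% to 0.5%. It does not depend on whether allocation is stratified.

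**2. Chance of county imbalance if allocation is unstratified with 12:12 fixed.** Let k be the number of Yang preschools in one arm. Then P(k) = C(14, k) × C(10, 12 − k) / C(24, 12), with C(24, 12) = 2,704,156.

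| Yang split | Probability (both directions) |
|---|---|
| 7:7 | 3432 × 252 / 2,704,156 = 0.320 |
| 8:6 | 2 × 0.2332 = 0.466 |
| 9:5 | 2 × 0.0888 = 0.178 |
| 10:4 or worse | 0.036 |

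So 9:5 or worse has probability 0.214, and 8:6 or closer has probability 0.786.

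**3. Shift in the arm difference.** Take preschools as equal in size. At 9:5, the Yang share is 9/12 in one arm and 5/12 in the other, a difference of 0.333. The unadjusted shift is 0.333 × county gap. The gap is an assumption, because the article gives no incidence by county.

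| Assumed gap (points) | Shift at 8:6 | Shift at 9:5 | 9:5 shift as share of 6 points |
|---|---|---|---|
| 3 | 0.5 | 1.0 | 17% |
| 6 | 1.0 | 2.0 | 33% |
| 10 | 1.7 | 3.3 | 56% |

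**4. Are these gaps compatible with the planned ICC?** Between-county variance is (14/24)(10/24) × gap² = 0.243 × gap². Dividing by 0.30 × 0.70 = 0.21 gives ICC contributions of about 0.001, 0.004 and 0.012. If 0.005 is the total ICC and county explained all of it, the largest possible gap is √(0.005 × 0.21 / 0.243) = 0.066, or 6.6 points. The 10-point row lies outside that limit.

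**5. Average loss of power.** This step assumes that 0.005 describes clustering within county only and that county is not adjusted for.

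- Effective number per arm: 3508 × 0.85 / 2 / 1.745 = 854.
- Planned standard error: √((0.21 + 0.1824) / 854) = 0.0214, giving power 80%.
- Standard deviation of the Yang share difference over all allocations: 0.206.
- Power = Φ(0.06 / √(0.0214² + (0.206 × gap)²) − 1.96).

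This gives about 77%, 68% and 52% for gaps of 3, 6 and 10 points. If 0.005 already includes county differences, the planned 80% already carries this cost. County control would then gain precision rather than restore it.

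**The case against.** The strongest reply is that the point rests on silence in a condensed article. A reader might infer that all 24 preschools are drawn from one unstratified list. The text does not say so. A separate sequence for each county fits the wording, and the even counts of 14 and 10 suit a stratified scheme equally well. The figures cited with the 12:12 statement were not available for this review and might show allocation by county. A reader might also infer that county is excluded from the model. That is not stated either: the socio-demographic set is open, and the full protocol or analysis plan could itemise it. Both replies stand, which is why the probabilities above are conditional on unstratified allocation.

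It can also be said that the size is assumed. No county difference is documented, and about 79% of unstratified allocations would be 8:6 or closer. At a 3-point gap the average cost is only about 3 points of power. This stands too. Baseline-injury adjustment would absorb part of a county difference. However, the baseline survey covers only the preceding 3 months against an 18-month outcome, so full recovery cannot be assumed.

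Finally, unstratified cluster randomisation is a valid design. That is correct, and nothing here contradicts a stated figure. What remains is that the article gives an allocation rule and an adjustment set, and neither, followed as written, controls a known site factor in a trial of 24 units.

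**Conclusion.** The point holds as a narrow design recommendation. No county stratification is stated and county is not a named covariate. If allocation is unstratified with 12:12 fixed, some county imbalance is more likely than not (68%), and a 9:5 or worse split in Yang occurs in 21% of allocations. The consequence is a shift of about 1 to 2 points at 9:5, against a 6-point target and before any adjustment, for assumed gaps of 3 to 6 points.

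Three stronger readings are not supported:

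- **Biased effect estimate.** Chance imbalance under valid randomisation costs precision and can distort the realised result, but it is not systematic bias.
- **A shift of half the planned effect or more.** That needs a gap near 10 points, which would by itself contribute about 0.012 to an ICC planned at 0.005.
- **A planned ICC that is too low.** The article does not say whether the cited value already includes differences between areas.

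The sample size of 3508 is unaffected.

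**What to change.** State whether allocation is stratified by county. If it has not yet been done, stratify: 7 of 14 preschools in Yang and 5 of 10 in Shicheng to each arm. This meets 12:12 exactly and needs only a small change to the randomisation program.

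Whether or not allocation is complete or was stratified, name county as a fixed effect in the primary GEE and in the confirmatory GLMM. The cost is one model term: with 24 preschools, the cluster-level degrees of freedom left after intercept and arm fall from 22 to 21. No change to the sample size or data collection is needed.
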